## Abstract

**Background:**

Lowering of blood pressure by antihypertensive drugs reduces the risks of cardiovascular events, stroke, and total mortality. However, poor adherence to antihypertensive medications reduces their effectiveness and increases the risk of adverse events. In terms of relative risk reduction, an improvement in medication adherence could be as effective as the development of a new drug.

**Methods/Design:**

The proposed randomized controlled trial will include patients with a low adherence to medication and uncontrolled blood pressure. The intervention group will receive a multifactorial intervention during the first, third, and ninth months, to improve adherence. This intervention will include motivational interviews, pill reminders, family support, blood pressure self-recording, and simplification of the dosing regimen.

**Measurement:**

The primary outcome is systolic blood pressure. The secondary outcomes are diastolic blood pressure, proportion of patients with adequately controlled blood pressure, and total cost.

**Discussion:**

The trial will evaluate the impact of a multifactorial adherence intervention in routine clinical practice. Ethical approval was given by the Ethical Committee on Human Research of Balearic islands, Spain (approval number IB 969/08 PI).

**Trial registration:**

Current controlled trials ISRCTN21229328

## Background

The prevalence of hypertension is about 35% for adults in general, about 40% for middle-aged individuals, and up to 68% for elderly individuals [1-3]. Most population-based studies confirm that hypertension increases the risk for cardiovascular events. For example, a recent meta-analysis indicated a continuous, strong, and graded relationship between blood pressure (BP) and the occurrence of atherosclerotic events [4]. Numerous antihypertensive agents can effectively lower BP and significantly reduce stroke, coronary heart disease, cardiovascular death and total mortality by 30-40%, 20-21%, 26-28%, and 13-16% respectively [5]. However, in clinical practice, hypertension can be difficult to control. It is estimated that only 40% of primary care hypertensive patients have BP below 140/90 mmHg, or below 130/80 mmHg for patients with diabetes or renal failure [6]. Clinical inertia and low adherence to medication are considered the major modifiable causes of poor BP control [7,8]. Adherence can be defined as the extent to which patients follow the instructions they are given for prescribed treatments. The prevalence of low adherence to antihypertensive drug therapy (AHT) has been estimated as 30-50% [9,10], and patients with poor adherence typically experience increased BP [11]. A report by the World Health Organization (WHO) addressed the general importance of improving adherence to long-term medical treatments [12]. The WHO report concluded that adherence is the result of a complex interaction of the social environment, patient, and healthcare professionals. It has also been reported that low adherence can increase the cost of treating hypertension by 15-20%, and is associated with more frequent hospitalization, use of emergency services, and admission to intensive care [13].

It has been shown that low adherence to long-term treatment often occurs when the treatment is complex or when the disease is asymptomatic (such as hypertension). Low adherence to AHT leads to reduced drug effectiveness and increased risk for the development of cardiovascular morbidities [10]. Moreover, adherence to AHT has been reported to reduce the risk of hospitalization by about 50%, and is also associated with reduced mortality [14,15].

Previous studies have reported that the poor adherence to AHT is due to patient perception that the disease is not significant, adverse drug effects, lack of treatment effectiveness, and the patient's poor or incomplete knowledge of the disease [16,17]. Clinical trials have shown that several strategies aimed at improving adherence to AHT were effective. A systematic review [18] indicated that the most effective interventions were simplification of dose regimens, reminder packaging, social and family support, BP self-registration, follow-up phone calls by nurses, teaching self-determination to patients, and graphical reminders for taking medication. Additionally, the use of multiple interventions is more effective than use of a single intervention.

The motivational interview, defined as a clinical patient-centered interview that helps to investigate and resolve ambivalence in unhealthy behaviors and/or habits to promote changes toward healthier lifestyles, is a recent method that can be used to promote behavioral changes in patients [19]. This process is more likely to be successful if the patient has a positive attitude about the need for change. Motivational interviewing is intended to help patients recognize and address their problems and to enhance their perception of treatment efficacy [20]. Optimal adherence to AHT depends largely on the relationship established between the healthcare professional and patient [21]. If the healthcare professional merely issues unilateral declarations about a treatment plan, the patient is less likely to adopt changes that have a positive impact on his/her health [22]. The motivation for change is greater if a patient and his/her healthcare professional work together to make treatment decisions. Additionally, patient outcome is better if the patient assumes responsibility for his/her own circumstances (locus of control) [23]. Clinical interviewing has been shown to be effective in the treatment of alcohol problems, drug addiction, smoking, obesity, and insufficient physical exercise.

The purpose of the present study is to evaluate the effectiveness of a multifactorial intervention that is designed to improve the systolic and diastolic BP of patients who have low adherence to AHT and elevated BP.

## Methods and Design

### Overview

Patients in a primary-care setting who have had low adherence to AHT, as assessed by the Morisky-Green or Haynes-Sackett tests, and elevated BP will be inform and ask to sign informed consent, those patients that agree to participate will be randomized equally to a "multifactorial intervention" group or a control group (which continued the usual care) (Figure 1). Participants in the intervention arm will receive three intervention sessions during a 9-month period. The intervention will be provided by study nurses who will have received special training for administration of motivational interviewing and in the implementation of the study protocol.

**Figure 1 F1:**
[figure not shown]
**Study design Flow-chart**.

Table 1 summarizes the measures and variables according to the timeline. Participants will be studied for 1 year following randomization. Primary and secondary outcomes will be assessed by an external nurse who will be blinded to treatment assignment after 12 months. The primary outcome will be systolic BP. Secondary outcomes will include diastolic BP, direct costs, and the number of patients who required treatment to yield one patient with normalized BP.

**Table 1 T1:** Measures, variables and timeline

VISIT	-1	0	1	2	3	4
Time (months)	-1	0	1	3	9	12
Blood pressure measurement inclusion criteria	X	X				
Morisky-Green and Haynes-Sackett tests	X					
Inclusion and exclusion criteria	X					
Comorbidities		X				
Blinded blood pressure measurement						X
Medication use						X
Adverse effects to medication		X				X
Medical consultation, cardiovascular events and hospital admission.						X
Checklist and time duration of intervention components (Intervention group)			X	X	X	
Motivational interview (Intervention group)			X	X	X	
Pill reminder (Intervention group)			X			
Family support (Intervention group)			X	X	X	
Blood pressure self-recording (Intervention group)			X	X	X	
Simplification of dosing regimens (Intervention group)			X			

Information bias will be minimized by use of a design that provides the maximum possible level of masking for studies of non-pharmacological intervention. In particular, the outcome assessor, data analyst, and physician will all be blinded to patient allocation. Misclassification, if any, is expected to be non-differential. Quality control will include recording of patient adherence to interventions, inclusion and follow-up monitoring, and quality supervision of data entry. We will perform an intention-to-treat analysis of the data; that is, the analysis will be by randomized assignment regardless of participation in intervention sessions.

### Study population

This study will enroll 320 patients, 18-75 years of age, who are being treated with AHT(s), remain hypertensive, and have low adherence to AHT as assessed by the Morisky-Green or Haynes-Sackett tests.

### Inclusion and exclusion criteria

The inclusion criteria are: age 18-75 years; poor BP control based on European Societies of Hypertension and Cardiology (ESH/ESC) guidelines (< 140/90 mmHg or < 130/80 mmHg in patients with diabetes or renal failure); and low adherence to medication as assessed by the Morisky-Green or Haynes-Sackett tests. The exclusion criteria are: presence of non-essential hypertension; treatment by hemodialysis; and institutionalization or terminal illness.

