### Randomization to treatment groups

The randomization sequence will be computer-generated, stratified by nurse and blocked in groups of two. Study nurses will call the research units to give patient identification numbers and will be told the randomly assigned patient allocations. After this, participants in the intervention group will be scheduled for their first intervention visits.

The outcome assessors, data analyst, and physician will be blinded to patient allocation. To evaluate the effectiveness of blinding, these individuals will be asked to choose the arm to which they believed each patient was assigned (possible answers: intervention, usual care, or unknown). If they answered "intervention" or "usual care", they were asked to indicate what led to that belief.

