### Multifactorial Intervention

The intervention consists of five components that will be delivered during three interventional visits of about 30 min each. Use of a detailed intervention protocol and comprehensive motivational interview training is intended to increase the effectiveness of interventions. The study nurses will carefully document each component of the multifactorial intervention that they perform by use of specially designed intervention visitation documents and will register the time and the duration of each component of the intervention.

The five components of the intervention are:

1. ***Motivational interview: ***This will be based on the Health Belief Model [24] and the Prochaska and DiClemente stage of change [25], and will try to resolve ambivalences that patients have regarding medication and explore perceptions that patients have about their ability to control events (locus of control).

2. ***Pillbox Reminder: ***A pillbox organizer with seven compartments will be given to the patients. They will self-fill it with one pill for each day of the week. Use of the pillbox will be explained to patients in the intervention group.

3. ***Family Support: ***Patients will designate one person in their household who will be responsible for reminding and monitoring medication intake. The designated person must accept responsibility of reminding the patient to take medication and of supervising pill intake. If a patient lives alone or does not wish to involve a family member or carer, they do not need to designate anybody. Thus, this part of the intervention is not mandatory.

4. ***BP measurements and AHT reminder forms: ***Twelve forms (one per month) and a table will be completed by the patient and nurse and used to record the date and hour of all BP readings (including gaps). AHT dosage and a telephone contact number will also be recorded on each form. This information will be frequently updated. The forms will be provided to patients and nurses at visit 0, and patients will be asked to bring them to all subsequent visits.

5. ***Simplification of dosing regimens: ***AHT dosage will be recorded at visit 0, and pharmacists will simplify the dosing regimen when possible at subsequent visits.

Visit 1 (first month, 40 min total): motivational interviewing (25 min), pill reminder (5 min), self-recording of BP (5 min), family support, when possible (5 min).

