An analysis of direct costs and outcomes for patients in both groups will be conducted by a nurse blinded to patient allocation. Clinical record review and detailed self-reported data on costs of healthcare utilization, clinical tests, and medication will be considered. All resources utilized will be multiplied by the appropriate cost using nationally applicable cost data. The cost of resource utilization (primary care visits, hospital admissions, clinical testing) will be estimated using the healthcare costs published in the *National Official Journal of Spain *or *Regional Officials Journal*. Costs of all AHTs will be calculated using prices published in the catalogue of pharmaceutical compounds by the Spanish Board of Pharmacists. Intervention costs will also consider the time needed to train nurses and the time of each intervention visit.

The primary health outcome for the cost analyses is BP reduction, which will be calculated using direct costs. The measure of "relative value for money" from the intervention is the incremental cost-effectiveness ratio calculated from the additional cost for a benefit of 1 mmHg reduction.

Analysis of costs may require variable transformation, but can be modeled using multivariate linear regression without a baseline value for costs because this value will be unknown. We will adjust for age, sex, and comorbidities that may affect cost. We recognize that we will have low statistical power to detect even moderate cost differences between the two groups.

Each nurse will provide intervention to a group of patients, so we will also measure the effect of individual nurses on outcome by multilevel analysis to determine if there is a significant variation across nurses that cannot be explained by random variation, also we will establish a number maximum of 10 patients per nurse to minimize this effect.

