### Limitations

Control patients are allowed to visit study nurses during the study period so "contamination" of the control group is possible. This would reduce the point estimate of the intervention's effectiveness and may lead to a type II error. In other words, an effective intervention could be classified as ineffective because the observed effect size was neither statistically nor clinically significant. We will try to overcome this problem by using a large sample size (n = 320) based on the assumption that there will be a 15% contamination rate.

Clinical inertia is an important factor associated with poor BP control [7]. As relevant to our study, physicians of the intervention patients may be more prone to change medications if they know that their patients are involved in a clinical trial of BP control. The possibility of this effect will be significantly reduced by blinding physicians to patient allocation. However because patients are not blinding to treatment, physicians could easily find out patient allocation. We will retrospectively review the medication records to determine if there were differences in the number of medication changes in the two treatment arms and we will evaluate the effectiveness of the blinding by direct interview. We will control in a multivariate analysis by number of medication changes and physicians blinding (yes/no).

There will be a tendency of BP values, when selecting patient non optimally controlled, to resemble their mean. Randomized trials with a control group avoid regression toward the mean because BP values fell in both treated and placebo groups, but it fell by more in the treated group.

In most non-pharmacological randomized controlled trials where follow-up visits are part of the intervention, follow-up visits in the control group are common. Thus, an undesirable "Hawthorne effect" could mask the effects of our intervention. To avoid this problem, the effects of the intervention will be compared with a control group without protocol-stipulated follow-up visits.

The ideal outcome measures for our trial are reduction of cardiovascular events and/or total mortality. However, such a study would be very expensive because it would require a very large sample size and very long study period. The use of clinically relevant reduction of BP (a surrogate marker) allows us to perform this study with a more manageable number of patients (n = 320) in a relatively short period of time (12 months).

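### Eligibility and randomisation allow two members of one household to land in opposite arms, so a control patient could be an intervention patient's designated supporter; the dilution is probably small and cheap to prevent

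*Protocol article*

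**What the plan says.** In the protocol article, Inclusion and exclusion criteria asks for age 18 to 75, poorly controlled blood pressure and low adherence, and then states: "The exclusion criteria are: presence of non-essential hypertension; treatment by hemodialysis; and institutionalization or terminal illness". Sharing a home with another participant is not mentioned.

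Randomization to treatment groups sets the allocation by patient: "The randomization sequence will be computer-generated, stratified by nurse and blocked in groups of two". Nurses phone the research unit for each allocation. No household rule appears here either.

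Under Multifactorial Intervention, the family support component reads: "Patients will designate one person in their household who will be responsible for reminding and monitoring medication intake". That person must agree to supervise pill-taking. For patients who live alone or prefer not to involve anyone, the section adds: "Thus, this part of the intervention is not mandatory".

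Limitations names one route of contamination: "Control patients are allowed to visit study nurses during the study period so 'contamination' of the control group is possible". The sample size section assumes 15% contamination and refers forward to that discussion. Statistical Analysis caps the nurse's list: "we will establish a number maximum of 10 patients per nurse to minimize this effect".

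**The concern.** The unit of randomisation is the patient, but one component is delivered through somebody else in the patient's home. Two cohabitants who are both treated, uncontrolled and poorly adherent can both meet the criteria as written, and may well share a primary-care nurse. If one is allocated to the intervention and the other to usual care, the control patient may be asked to remind and supervise the other's pill-taking, and may see the pillbox and the recording forms in daily use. The Control group section intends no change in care for that patient.

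Any such exposure would pull the arms together and bias the systolic blood pressure difference towards zero. The protocol already regards dilution as a threat, and says in Limitations that it may produce a type II error. What it does not consider is this route. Once a split household has been enrolled, the exposure cannot be undone in the analysis.

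**Working it through.** **1. The plan's own contamination figures.** The sample size section gives 110 per group (220 in total), a factor of 1.41 for 15% contamination, and a final target of 320.
- The usual dilution factor is 1/(1 − c)². With c = 0.15 it is 1/0.85² = 1.384, close to the stated 1.41 but not equal to it.
- 220 × 1.41 = 310.2, and 220 × 1.384 = 304.5. The target of 320 is above both.
- 320/220 = 1.4545 corresponds to c = 1 − √(220/320) = 0.171. Taking the 220 as given, 320 absorbs about 17% total contamination.

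**2. Chance that two household members are split.** Inputs: individual 1:1 allocation, blocks of two within nurse, at most 10 patients per nurse (five blocks). Two patients in the same block are split with probability 1; in different blocks, or under different nurses, with probability 0.5.
- Unrelated positions in a list of 10: 45 pairs, 5 within a block and 40 across. (5 × 1 + 40 × 0.5)/45 = 25/45 = 5/9 = 55.6%.
- Consecutive enrolment in a list of 10: 9 adjacent pairs, 5 within a block and 4 across. (5 × 1 + 4 × 0.5)/9 = 7/9 = 77.8%.
- Shorter lists raise the figure for unrelated positions: 60% with 6 patients, 66.7% with 4.
- Different nurses: 50%.

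**3. Controls who would live with an intervention patient.** Let h be the share of participants who live with another participant. The document gives no value, so 2%, 5% and 10% are assumptions. Couples = 320h/2. Exposed controls = couples × split probability, taken from 0.5 to 7/9 and divided by 160 controls.

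**4. Upper bound on the consequence.** Suppose every exposed control receives the full intervention effect, on top of the 15%. With exposed share e, c = 0.15 + 0.85e. The N needed is 220/(1 − c)². Power at 320 uses 320 × 0.8/2 = 128 evaluable per arm, a difference of 6(1 − c) mmHg and an SD of 15 mmHg: Φ[6(1 − c)/(15√(2/128)) − 1.96]. At c = 0.15 this is Φ(5.1/1.875 − 1.96) = 77.6%.

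| h (assumed) | Couples | Exposed controls | Share of 160 | c | N needed | Power at 320 |
|---|---|---|---|---|---|---|
| 0 | 0 | 0 | 0 | 0.15 | 304.5 | 77.6% |
| 2% | 3.2 | 1.6–2.5 | 1.0–1.6% | 0.1585–0.1632 | 311–314 | 76–77% |
| 5% | 8 | 4.0–6.2 | 2.5–3.9% | 0.1712–0.1831 | 320–330 | 74–76% |
| 10% | 16 | 8.0–12.4 | 5.0–7.8% | 0.1925–0.2161 | 337–358 | 71–73% |

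On this bound, the margin in 320 is used up at about 5% co-enrolment.

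**5. Within-household correlation.** For n per arm and correlation ρ within a couple, the variance of the difference in means is (2σ²/n)[1 − ρ(split − unsplit)/n]. Take 16 couples, 7/9 of them split (12.4 against 3.6), an assumed ρ of 0.2 and n = 160. The correction is 0.2 × 8.8/160 = 0.011. An analysis that treats them as independent overstates the variance by about 1%, which is conservative.

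**The case against.** The strongest case against is that nothing in the text is contradictory. The eligibility list is merely silent on cohabitants, and a condensed article may leave enrolment detail to a full protocol. The protocol already inflates the sample for 15% contamination and admits the risk of dilution. Co-enrolment may be rare: both people must be treated, uncontrolled, poorly adherent and willing, and 320 patients at no more than 10 per nurse means at least 32 nurses. At 2% co-enrolment even the upper bound needs only 311 to 314 patients.

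Much of this stands, and it rules out several stronger readings that a reader might infer.
- That household components do reach controls. The document shows only that they could. Family support is optional and directed at the index patient. The pillbox is that patient's own, the forms carry that patient's own dosage, and the motivational interview and dose simplification are individual.
- That blocks of two usually split households. The 7/9 figure needs the same nurse and consecutive enrolment; across nurses the chance is no higher than under any 1:1 allocation.
- That treating cohabitants as independent gives false precision. For split couples the error runs the other way and is negligible.
- That total contamination will exceed 15%. Nothing in the document shows this, and living with an intervention patient is not the same as being fully contaminated.

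The objection does not remove the gap itself. The eligibility criteria and the allocation procedure are both set out, and as set out they admit split households. The 15% is justified only by nurse contact, so it cannot be read as an allowance for this route. If the full protocol already carries a household rule, the point falls away.

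**Conclusion.** The point holds as a cheap improvement of small expected size. As written, the protocol permits a control patient to be the household supporter of an intervention patient, and blocks of two within nurse make a split more likely than not for cohabitants who share a nurse. The direction is dilution towards no difference, by a route that Limitations does not consider.

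At an assumed 2% to 10% co-enrolment, about 1% to 8% of controls would be exposed. If every one of them were fully contaminated in addition to the 15%, power at 320 would fall from 77.6% to between 71% and 77%. The true loss is likely to be well below that bound. These figures assume two-person households, equal arms and the protocol's 220 as the base. The co-enrolment rate is the one input that matters most, and the document does not give it.

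**What to change.** Add to Inclusion and exclusion criteria an exclusion for anyone living in the same household as a patient already randomised in this trial. State in Randomization to treatment groups that only one member of a household may be randomised. The research unit can ask the nurse to confirm this on the phone call that already precedes each allocation.

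The cost is one criterion, one question on an existing call, and the loss of a few otherwise eligible cohabitants: one per couple, so about 3, 8 or 16 people at 2%, 5% or 10% co-enrolment, to be replaced by other recruits. Randomising households as a unit would also close the route, but it changes the allocation scheme and is more work for the same gain. If enrolment has begun, record which participants share a home and report how many households were split.
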